## **13.0 DATA HANDLING**

### **13.1 Data Collection and Record Keeping at the Study Site**

Data Collection: All study data will be collected by the clinical study staff using designated source documents and entered onto the appropriate case report forms (CRFs). CRFs will be provided by IAVI and should be handled in accordance with the instructions from IAVI. All study data must be verifiable to the source documentation. A file will be held for each volunteer at the clinic(s) containing all the source documents. Source documentation will be available for review to ensure that the collected data are consistent with the CRFs.

All CRFs and laboratory reports will be reviewed by the clinical team, who will ensure that they are accurate and complete.

Source documents and other supporting documents will be kept in a secure location. Standard GCP practices will be followed to ensure accurate, reliable and consistent data collection.

*Source data include but are not limited to:*

- Signed Informed Consent Documents
- Dates of visits including dates of vaccinations
- Documentation of any existing conditions or past conditions relevant to eligibility
- Reported laboratory results
- All adverse events
- Concomitant medications
- Local and systemic reactogenicity events

### **13.2 Data Entry at the Study Site**

The data collected at the study site will be recorded on the CRFs by the study staff. All clinical trial information collected will be entered into a database. To provide for real time assessment of safety, data should be entered into the database as soon as reasonably feasible after a visit occurred.

### **13.3 Data Analysis**

The data analysis plan will be developed and agreed upon by the Sponsor, PIs and Collaborating Companies prior to unblinding of the study. The statistician at the Data

Coordinating Centre (DCC), in collaboration with the Principal Investigators, Sponsor, and Collaborating Companies will create tables according to this data analysis plan.

The DCC will conduct the data analysis and will provide interim and final study reports for the Sponsor, Principal Investigator, the SRB and the regulatory authorities, as appropriate.

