| EVALUATION FOR INTER-CURRENT HIV INFECTION:       | 
Volunteers will be tested for HIV according to the Schedule of Procedures. Test results will be interpreted according to a pre-determined diagnostic algorithm. Should one or more serological HIV test(s) post-vaccination be positive, a nucleic-acid-based HIV test will be performed to distinguish a true HIV infection acquired through exposure in the community from HIV seropositivity due to the vaccine-induced antibody response. HIV testing at additional time points may be performed upon request of the volunteer and principal investigator or designee as medical or social circumstances warrant.
 
To maintain blinding of study staff with direct contact with the volunteers, HIV test results will be reported to the clinical team as “HIV-uninfected” or as “HIV-infected” (ONLY once intercurrent HIV infection is confirmed).
                                                                                                                                                                                                                                                  |
| SAFETY MONITORING AND STATISTICAL CONSIDERATIONS: | 
All clinical trial data collected, identified only by a volunteer identification number, will be entered into a database.
 
Safety will be continually monitored by the Investigators, the Sponsor’s Medical Monitor and a Protocol Safety Review Team (PSRT); detailed stopping criteria are pre-defined.
 
All safety data will be reviewed by an independent Safety Review Board (SRB) once the first 15 volunteers randomized across all groups have reached the M 2.5 and M 6.5 time points.
 
Ad-hoc safety review may be specifically requested by the Sponsor, Profectus, Ichor, the Principal Investigators, Ethics Committees, Regulatory Authorities, or by the SRB.
 
At the end of the study, a full analysis will be prepared according to a pre-specified statistical analysis plan. In addition, there may also be interim reviews of blinded data. All clinical and routine laboratory data will be included in the safety analysis. Immunogenicity analysis will be performed according to a predefined analysis plan for all volunteers who received vaccine or placebo.
 |

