**Table 14.3-2: Comparison of 2 vaccine groups**

| # Vols
per group | Rate of events in one group |     |     |     |
|---------------------|-----------------------------|-----|-----|-----|
|                     | 5%                          | 10% | 20% | 30% |
| 12/12               | 56%                         | 58% | 59% | 59% |
| 24/12               | 48%                         | 50% | 52% | 51% |

The current sample size will achieve 80% power, at  $\alpha=5\%$ , to detect the above differences in event rates between individual or combined groups. The calculations are based on Fisher's exact 2-tailed test, using PASS 2008.

One or more descriptive interim analyses of grouped data may be carried out without unblinding the study to investigators or volunteers. At the end of the study, a full analysis will be prepared according to a pre-specified SAP.

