### *Immunogenicity*

Cellular immune responses will be analyzed and compared using binomial methods (Fisher's exact test) to examine for the presence or absence of HIV specific T-cell responses quantified by ELISPOT and ICS. Assays will be performed using the IAVI, HIL, and CRC SOPs and standard reagents for all volunteers.

Presence or absence of antibodies to the vaccine-based HIV gene products will be also analyzed. Assays will be performed in a similar fashion in all volunteers.

A descriptive interim analysis may be performed when all volunteers in a given group have reached one month post boost.

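### The protocol's deadline for the analysis plan does not secure that the plan is fixed before group-level immunogenicity results can be seen

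*Protocol*

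**What the plan says.** The plan's deadline is in protocol section 13.3: "The data analysis plan will be developed and agreed upon by the Sponsor, PIs and Collaborating Companies prior to unblinding of the study". The same section says that the Data Coordinating Centre (DCC) "will provide interim and final study reports for the Sponsor, Principal Investigator, the SRB and the regulatory authorities, as appropriate".

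Section 14.3, below Table 14.3-2, adds: "One or more descriptive interim analyses of grouped data may be carried out without unblinding the study to investigators or volunteers". Its Immunogenicity paragraph gives a trigger for each group: "A descriptive interim analysis may be performed when all volunteers in a given group have reached one month post boost". For the end of the trial, 14.3 says: "At the end of the study, a full analysis will be prepared according to a pre-specified SAP". The synopsis, under safety monitoring and statistical considerations, says: "In addition, there may also be interim reviews of blinded data". It also promises a predefined plan for immunogenicity, without a date.

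Section 7.8 blinds study staff and volunteers to vaccine versus placebo and to IL-12 dosage. Schedule, number of vaccinations and delivery method stay open. The three secondary objectives in 4.2 all compare groups on immune responses. For cellular responses, 14.3 names Fisher's exact test "to examine for the presence or absence of HIV specific T-cell responses quantified by ELISPOT and ICS".

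**The concern.** A plan counts as pre-specified if it was fixed before anyone who shapes it could see the comparison it governs. Section 13.3 ties sign-off to unblinding of the study. Section 14.3 describes the interim summaries as leaving investigators and volunteers blinded, so on a plain reading they do not trigger that deadline.

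The secondary contrasts are between groups, and each group has 12 vaccine and 3 placebo recipients. A group summary that pools the two is still 12/15 = 80% vaccine recipients. If placebo response rates are alike across groups, a true difference between two groups' vaccine recipients shows at 0.8 of its size. Keeping vaccine and placebo masked within a group therefore hides little of the contrast.

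At stake is whether the secondary immunogenicity conclusions can be called pre-specified. Several assays and visits could serve each objective, and a choice made after group results are known would not have the nominal error rate.

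**Working it through.** **1. The protocol's own figure.** Table 14.3-2 gives detectable differences of 56%, 58%, 59% and 59% for 12 versus 12 (two-tailed Fisher, alpha 5%, 80% power) at rates of 5%, 10%, 20% and 30%. Exact enumeration of Fisher's test over two binomials gives power of 80.0%, 79.3%, 79.4% and 80.6% at those differences. The row reproduces. The point does not rest on it; it only confirms the Fisher calculation used below.

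**2. Timing (Appendices A and B).**
- Groups 4-5: one month post boost is D140 and the last visit is D336. 336 − 140 = 196 days = 28 weeks.
- Groups 1-3: one month post boost is D196. 336 − 196 = 140 days = 20 weeks.

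Because the trigger waits for everyone in the group, these are also about the shortest gaps between the interim and that group's last visit.

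**3. Which contrasts are exposed (4.2, 7.8).**
- Objective 3, Group 4 v 5: both groups reach D140 on the same schedule, and the order of electroporation and plain injection tells them apart. No code has to be broken.
- Objective 2, three primes v one: the schedule separates Group 4 from Groups 1-3, but Group 3 must also be shown apart from Groups 1 and 2.
- Objective 1, IL-12 dosage: Groups 1-3 share schedule and delivery method. Coded labels could protect this contrast, but the protocol does not require them.

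**4. How many candidate tests exist by the trigger.** Section 5.1.2 lists ELISPOT, ICS CD4+ and ICS CD8+: 3 readouts. Post-boost PBMC draws by the trigger are D175, D182 and D196 (Groups 1-3) or D119, D126 and D140 (Groups 4-5): 3 visits. 3 × 3 = 9 per contrast.

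**5. What selection could do.** Assume no true difference, 12 v 12 and two-tailed Fisher at 5%. The responder rate p and the within-person correlation rho are assumptions, because the protocol gives neither for this regimen.
- One pre-named test: the exact size s is the sum of the two-binomial probabilities over tables with p-value ≤ 0.05.
- Best of nine, rho = 0: 1 − (1 − s)^9.
- Best of nine, rho = 0.9: simulation with a latent-normal model, counting runs in which any of the nine tests rejects.

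| p | one test, s | best of 9, rho = 0 | best of 9, rho = 0.9 |
|---|---|---|---|
| 33% | 1.8% | 1 − 0.9816^9 = 15.4% | 8.5% |
| 50% | 2.3% | 1 − 0.9772^9 = 18.8% | 10.1% |
| 80% | 1.2% | 1 − 0.9881^9 = 10.2% | 5.9% |

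So about 1-2% becomes about 6-19% per contrast.

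**The case against.** The best reply is that 13.3 implies the right order. The plan is agreed, the DCC statistician then builds tables from it, and the next paragraph speaks of interim and final reports. The words pre-specified and predefined elsewhere point the same way. This shows intent and makes abuse less likely, but none of these statements sets a date earlier than unblinding.

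A second reply is that the interims may never show results by group. Grouped data can mean aggregated data, the synopsis speaks of blinded data, and a trigger for one group does not say what is displayed. Labelled results sent to the Sponsor might themselves count as unblinding, and reports go out only as appropriate. This stands in part. By-group display is the likelier reading of a group-by-group trigger, but not the only one. The protocol neither requires pooling or coded labels nor says whether the Sponsor stays blinded.

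Third, the interims are optional and descriptive, and no interim test or adaptation is planned. That is correct, and it limits the weight of the point.

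Fourth, naming the deciding readout and visit is ordinary SAP content. That is also correct. Their absence from the protocol is not a fault; the fault is the date by which they must be settled.

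**Conclusion.** The point holds as a gap in a stated rule. The deadline in 13.3 can be met after group-level immunogenicity summaries have reached people who agree the plan. The possible effect is a rise in the false-positive rate per contrast from about 1-2% to about 6-19%. That rests on nine candidate tests, responder rates of 33-80%, correlation of 0-0.9, and selection of the best result. It is what selection could produce, not a forecast. The primary endpoints are safety endpoints and are untouched. A SAP signed early would cure the practice, though not this text.

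A reader might infer more, and the documents do not support it:
- That the readout will be chosen after the fact: the text only fails to prevent it.
- That the chance of some false claim across all the pairwise contrasts is the right measure: that mixes in multiplicity which exists whatever the sign-off date.
- That the larger inflation of a t-test on magnitude applies: the test named in 14.3 for cellular responses is Fisher's on presence or absence.
- That post-prime and post-boost visits would give opposite answers: nothing in the protocol shows this, and the objectives concern complete prime-boost regimens.

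This is a cheap improvement, not a threat to the trial.

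**What to change.** In 13.3, replace the deadline with wording such as: *The analysis plan, including the deciding immunogenicity readout and visit for each secondary between-group contrast, will be agreed before the first interim summary of immunogenicity data by group is released to anyone who agrees the plan, and in any case before unblinding.*

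The readout and visit can stay in the SAP; only the date belongs in the protocol. The Safety Review Board's safety reviews are not tied to this date and go ahead as planned.

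The change is one sentence and needs no added volunteers, visits or assays. Its cost is that the plan must be finished earlier, and ideas that arise after the first by-group summary become exploratory.

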## **14.0 STATISTICAL CONSIDERATIONS**

### **14.1 Sample Size**

A total of 75 volunteers (60 vaccine/15 placebo) will be enrolled into 5 groups.

### **14.2 Null Hypothesis**

The null hypothesis is based on the primary outcome variables, which are all safety parameters. Let  $\pi_0$  and  $\pi_1$  be the proportions of placebo and vaccinated volunteers, respectively, with a primary event. Then the hypothesis is:

$$H_0: \pi_0 = \pi_1 \text{ versus } H_1: \pi_0 < \pi_1$$

i.e., a 1-tailed test of whether the proportion of vaccinated volunteers with an event is greater than the proportion of placebo volunteers with an event.

### **14.3 Statistical Power and Analysis**

#### *Safety and Tolerability:*

The rate of local and systemic reactogenicity will be used to assess the differences between vaccine regimens.

The rate of SAEs causally related to the Investigational Product will be used as one measure of the safety of the Investigational Product. AEs that may be temporarily incapacitating (for example, loss or cancellation of work or social activities), which could make an Investigational Product impractical for large scale use if they occur in more than a small proportion of cases, will also be assessed.

All adverse events will be reported, grouped by seriousness, severity and relationship to the Investigational Product (as judged by the investigator).

For any event (e.g., severe AE, SAE related to IP): if none of the volunteers receiving the combination of Investigational Products experiences such an event, then the 2-sided 95% upper confidence limit (CL) for the rate of these events in the population (by the Clopper Pearson method) is 0.06 (n=60) and 0.265 (n=12).

The current sample size will achieve 80% power, at alpha=5%, to detect the following differences in event rates between groups. The calculations are based on Fisher's exact 1-tailed test, using PASS 2008 ([www.ncss.com](http://www.ncss.com)).

**Table 14.3-1: Vaccine versus Placebo**

| # Vols
Vaccine/ Placebo | Rate of events in the placebo group |     |     |     |
|----------------------------|-------------------------------------|-----|-----|-----|
|                            | 1%                                  | 5%  | 10% | 20% |
| 12/3                       | 80%                                 | 80% | 81% | 78% |
| 24/6                       | 53%                                 | 57% | 59% | 59% |
| 60/15                      | 27%                                 | 31% | 34% | 38% |

For example, if the true rate of events in placebo recipients (n=15) is 5%, then 60 volunteers receiving vaccine will provide 80% power to detect a statistically significant difference of 31% or more (i.e., a rate of  $\geq 36\%$ ).

**Table 14.3-2: Comparison of 2 vaccine groups**

| # Vols
per group | Rate of events in one group |     |     |     |
|---------------------|-----------------------------|-----|-----|-----|
|                     | 5%                          | 10% | 20% | 30% |
| 12/12               | 56%                         | 58% | 59% | 59% |
| 24/12               | 48%                         | 50% | 52% | 51% |

The current sample size will achieve 80% power, at  $\alpha=5\%$ , to detect the above differences in event rates between individual or combined groups. The calculations are based on Fisher's exact 2-tailed test, using PASS 2008.

One or more descriptive interim analyses of grouped data may be carried out without unblinding the study to investigators or volunteers. At the end of the study, a full analysis will be prepared according to a pre-specified SAP.

### *Immunogenicity*

Cellular immune responses will be analyzed and compared using binomial methods (Fisher's exact test) to examine for the presence or absence of HIV specific T-cell responses quantified by ELISPOT and ICS. Assays will be performed using the IAVI, HIL, and CRC SOPs and standard reagents for all volunteers.

Presence or absence of antibodies to the vaccine-based HIV gene products will be also analyzed. Assays will be performed in a similar fashion in all volunteers.

A descriptive interim analysis may be performed when all volunteers in a given group have reached one month post boost.

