### 3.3 Experience with recombinant human IL-12 pDNA as molecular adjuvant for HIV pDNA vaccines

No clinical studies have yet been conducted testing HIV-MAG vaccine co-administered with GENEVAX® IL-12.

However, other HIV-1 pDNA vaccines expressing antigens similar to HIV-MAG have been tested in Phase 1 clinical studies in combination with GENEVAX® IL-12. The NIH-sponsored clinical trials (HVTN 060, 063, 070) in which different candidate HIV-1 pDNA vaccines co-administered with the GENEVAX® IL-12 given intramuscularly (IM) by needle injection were tested in approximately 250 healthy HIV-uninfected adults. No major safety concerns have been noted in these studies.

In HVTN 080, an HIV-1 pDNA vaccine (PENNVAX™-B gag, pol, env) mixed with GENEVAX® IL-12 was administered IM by *in vivo* electroporation (EP) using Inovio's Celectra device. Final safety data are not yet available, but no major safety concerns have been reported. Preliminary

immunogenicity data from HVTN 080 indicate that IL-12 increases the frequency of immune responses to the HIV-1 proteins as measured by ICS (CD4+: 81%, CD8+: 52% with IL-12 versus CD4+: 44%, CD8+: 33% without IL-12) 2 weeks post 3rd administration of PENNVAX™-B and GENEVAX® IL-12.

Please see the Profectus Biosciences Inc. (PBS) HIV-MAG – IL12 Investigator Brochure (Version 2.0, May 2011) for a full description of the preclinical and/or clinical safety profile of the HIV-MAG vaccine and the IL-12 pDNA as molecular adjuvant.

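### Naming Boschloo's exact test instead of Fisher's for T-cell response rates would gain power at 12 per group at no cost in volunteers: a cheap improvement, not an error

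*Protocol*

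**What the plan says.** The statement that fixes an analysis method is in Protocol section 14.3, under Immunogenicity: "Cellular immune responses will be analyzed and compared using binomial methods (Fisher's exact test"), applied to the presence or absence of HIV-specific T-cell responses by ELISPOT and ICS. It gives neither a significance level nor a sidedness.

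Fisher's test also appears twice as the basis of power calculations. For vaccine against placebo, section 14.3 says "The calculations are based on Fisher's exact 1-tailed test". For two vaccine groups, the text below Table 14.3-2 says "The calculations are based on Fisher's exact 2-tailed test, using PASS 2008", with alpha 5%; there, "The current sample size will achieve 80% power" refers to the tabulated differences in event rates. On size, section 14.1 says: "A total of 75 volunteers (60 vaccine/15 placebo) will be enrolled into 5 groups". Each group has 12 vaccine and 3 placebo recipients (Table 5.2-1).

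Section 3.3 quotes preliminary ICS response rates from an earlier Phase 1 study of a different DNA vaccine: "CD4+: 81%, CD8+: 52% with IL-12 versus CD4+: 44%, CD8+: 33% without IL-12".

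**The concern.** With 12 volunteers per group there are only 13 x 13 possible outcomes, and Fisher's test also conditions on the total number of responders. Its attainable p-values are therefore coarse, and its true error rate lies well below the nominal level. The unused error is lost power.

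Secondary objective 1 (section 4.2) asks whether IL-12 increases HIV-specific responses and at which dosage level. Part of the evidence will come from comparing responder proportions between groups of 12, or between combined groups of 24 and 12. Power is scarce in such comparisons. An exact test with the same 5% guarantee and never less power is available, and because the protocol itself names Fisher's test, the choice is not simply left open for the statistical analysis plan.

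**Working it through.** **Inputs.** Groups of 12 v 12 and 24 v 12 (Table 14.3-2); two-sided alpha of 5% (text below that table, borrowed because the Immunogenicity paragraph states none); illustrative response rates from section 3.3.

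**Formulas.** Let a and b be the responders among n1 and n2 volunteers, and R the set of tables (a, b) that a test rejects.
- Power(p1, p2) = sum over R of C(n1,a) p1^a (1-p1)^(n1-a) x C(n2,b) p2^b (1-p2)^(n2-b).
- Size = maximum over a common rate p of Power(p, p), taken on a 2,000-point grid.
- Fisher's region: all tables with two-sided Fisher p <= 0.05.
- Boschloo p-value of a table: maximum over p of the probability of a Fisher p-value no larger than the one observed. Its region: all tables where this is <= 0.05.

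**Why Boschloo's test cannot lose power.** Fisher's p-value is valid at every common rate, so the probability of a Fisher p-value at or below some value never exceeds that value. The Boschloo p-value is therefore never larger than Fisher's, and every Fisher rejection is kept.

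**Reproducing the plan.** For the 12/12 row of Table 14.3-2 at base rates 5/10/20/30%, the table gives 56/58/59/59 points. Enumeration with Fisher's two-sided test gives 56.0/58.4/59.4/58.7. The row reproduces.

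**Size, two-sided nominal 5%.**

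| Groups | Fisher maximum | Boschloo maximum |
|---|---|---|
| 12 v 12 | 2.28% | 4.49% |
| 24 v 12 | 2.95% | 4.49% |

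At 12 v 12, Fisher's maximum occurs at a common rate of 50%. Its size is 1.72% at 30%, 1.19% at 20% and 0.25% at 10%.

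**Where the difference lies.** At 12 v 12, Fisher's test rejects 60 tables. Boschloo's rejects the same 60 plus 12 more: 0 v 4, 1 v 6, 2 v 7, 5 v 10, 6 v 11, 8 v 12 and their mirror images. For 0 v 4, Fisher's p = 2 x C(12,4)/C(24,4) = 2 x 495/10,626 = 0.093, while Boschloo's is 0.045. For 1 v 6 the values are 0.069 and 0.029.

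**Power at the differences stated in the 12/12 row.**

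| Base rate | Stated difference | Fisher | Boschloo |
|---|---|---|---|
| 5% | 56 | 80.0% | 89.9% |
| 10% | 58 | 79.3% | 87.5% |
| 20% | 59 | 79.4% | 83.3% |
| 30% | 59 | 80.6% | 87.8% |

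The difference detectable at 80% power with Boschloo's test is 48.1/52.0/56.9/55.2 points.

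**Illustration with the rates in section 3.3.** In the 24 v 12 rows the larger group has the higher rate, as it would if Groups 2 and 3 were combined against Group 1.

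| Contrast | Groups | Fisher | Boschloo |
|---|---|---|---|
| CD4+, 81% v 44% | 12 v 12 | 33.2% | 45.1% |
| CD4+, 81% v 44% | 24 v 12 | 49.9% | 60.0% |
| CD8+, 52% v 33% | 12 v 12 | 8.7% | 13.2% |
| CD8+, 52% v 33% | 24 v 12 | 14.0% | 15.3% |

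**Safety contrast, only if Fisher's test is used there.** For 60 v 15, one-tailed at 5%, the maximum size is 2.93% with Fisher's test and 4.99% with Boschloo's. In the protocol's worked example (5% v 36%), power goes from 79% to 87%.

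**The case against.** Fisher's test controls the error rate, section 14.3 names it consistently, and the 12/12 row of Table 14.3-2 reproduces with it. Preferring a less conservative exact test is partly a matter of taste, and statisticians who favour conditional inference will disagree. That stands: nothing in the protocol is misstated, and the point is one of efficiency.

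Three stronger readings are tempting, and the document supports none of them.
- A reader might infer that Fisher's test is also fixed for the final safety comparison. Section 14.3 names it only for the safety power calculations, and section 14.2 specifies a one-tailed hypothesis without naming a test. The full analysis is left to a statistical analysis plan that is not shown.
- A reader might take the 2.3% as a property of the planned immunogenicity analysis. It depends on a two-sided 5% level that the Immunogenicity paragraph does not state.
- A reader might equate the power of this test with the power of secondary objective 1. That objective concerns immune responses generally, and section 5.1.2 lists magnitude as well as frequency, so responder proportions are only one route to it.

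The practical gain is also uneven. It is appreciable for the CD4+ contrast and slight for CD8+. The rates are preliminary and come from another DNA vaccine and electroporation device, two weeks after a third DNA dose and with no Ad35 boost (sections 3.1 and 3.3). They are not planning assumptions of this trial.

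Finally, the added power comes from using more of the error allowance. At 12 v 12 the maximum false-positive rate per comparison roughly doubles, from 2.3% to 4.5%. It stays within 5%, but the trade-off is real where several groups and assays are compared.

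What survives is that the protocol fixes a test for response rates, and a test with the same guarantee and never less power exists at the same sample size.

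**Conclusion.** This is a worthwhile, low-priority improvement. Assuming two-sided testing at 5%, Fisher's test uses at most 2.3 of the 5 points of error allowed at 12 v 12, and at most 3.0 at 24 v 12; Boschloo's uses up to 4.5 in both. At the 12/12 differences in Table 14.3-2 the gain is about 4 to 10 points of power. At the illustrative rates it is 10 to 12 points for CD4+ and 1 to 5 for CD8+. No illustrated contrast reaches 80%, so the change does not remedy the small group size; it only stops the test from giving up power that the design already has.

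**What to change.** In section 14.3, under Immunogenicity, name Boschloo's exact unconditional test, two-sided at 5%, as the primary test for binary cellular-response comparisons between vaccine groups, and report Fisher's p-value as a sensitivity analysis. Carry this into the data analysis plan, which section 13.3 already requires to be agreed before unblinding. The Fisher-based tables in section 14.3 can stand as conservative planning figures. If the final safety comparison is also to use Fisher's test, the same substitution may be made there, one-tailed.

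The cost is a sentence of analysis wording and a standard software routine, with no extra volunteers. The downsides are a less familiar test and an actual false-positive rate per comparison that moves closer to the nominal 5% without exceeding it.
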